# Measurement/Data collection tools

1. Household survey

Clusters (villages) will be systematically surveyed (EPI cluster survey methodology), the aim being to identify 20 children per village with an active case of childhood diarrhea until the desired sample size is obtained. Villages will be enumerated and then randomly selected. Following verbal consent, a trained interviewer will complete the questionnaire. A follow-up endline survey, also of active cases of childhood diarrhea, using the same questionnaire will be carried out six months following the baseline.

Interviewers will use a pictograph to assist parents in identifying drugs used. The study investigators will subsequently categorize them.

2. In-depth interviews with providers

## The primary aim of the interviews is to better understand diarrhoea management practices in relation to facilitating factors and important barriers to adhering with WHO/UNICEF diarrhoea management guidelines. This will include the influence of drug salesmen, financial incentives, and perceptions of what licensed providers are practicing. Assessment of these factors will be stratified by important provider characteristics, such as age, type of provider and location.

## Conduct of study and timetable

**Period: 8 Months**

| **Activities** | **Months** | | | | | | | |
| --- | --- | --- | --- | --- | --- | --- | --- | --- |
| **1** | **2** | **3** | **4** | **5** | **6** | **7** | **8** |
| Recruitment & Training of  Research staff |  |  |  |  |  |  |  |  |
| Training of SACMOS |  |  |  |  |  |  |  |  |
| Baseline Survey |  |  |  |  |  |  |  |  |
| Training of Private providers |  |  |  |  |  |  |  |  |
| Follow up Support |  |  |  |  |  |  |  |  |
| End line Survey |  |  |  |  |  |  |  |  |
| Analysis, write-up &  dissemination |  |  |  |  |  |  |  |  |

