# Description of the Research Project

## Hypothesis to be Tested:

Concisely list in order, the hypothesis to be tested and the Specific Aims of the proposed study. Provide the scientific basis of the hypothesis, critically examining the observations leading to the formulation of the hypothesis.

That an NGO initiated sensitization, training and support package to scale up the prescribing of

zinc among NGO and private sector providers for the treatment of acute childhood diarrhea will,

within 4 months, result in:

H1. A significant increase in zinc coverage for the treatment of children under five years of age

within the NGO catchment population, and

H2. A significant decrease in the use of antibiotics and antidiarrhoeals

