## Study populations

1. Care takers of the children aged 6 months to 5 years with a prevalent case of diarrhea at the

time of the household surveys (within the past 2 weeks). Within each site a systematic household

survey will be completed for the identification of any child 6 months to 5 years who has a

prevalent case of at least 2 days duration.

2. Health Care Providers

1. NGO licensed “sub-assistant community medical officers (SACMOs)
2. Private sector, unlicensed providers: village practitioners and traditional healers

There are eight SACMOs and one medical officer posted at static and satellite clinics per two unions. Within each site a census will be carried out to enumerate all private sector providers by type. 10 of each type will be randomly selected to complete in-depth interviews.

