## Intervention Package:

- Training/orientation on diarrhea case management
- Follow-up health provider support

ICDDR,B will first train the trainers, i.e. the NGO health care providers who will implement the intervention package. These individuals will then conduct the training and support of other NGO staff and private unlicensed providers.

[note: we would have liked to include licensed providers, but the #s are insufficient]

The training/orientation materials to be used are summarized in the box below:

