###### Orientation package/training program

For DSK Health care providers (MBBS & SACMO): provided by ICDDR,B study staff

- Refresher course and up-date on WHO/UNICEF guidelines for treatment of childhood diarrhoea
- Training videos (docu-drama)
- Orientation/training materials (zinc babohar nirdeshika)
- Frequently asked questions booklet
- Follow-up support

For 1st line community health care providers (Village practitioner, drug venders, traditional healers): provided by DSK SACMO trainers

- Orientation/training materials (flip chart, zinc babohar nirdeshika)
- Training videos (docu-drama)
- Zinc commercial (mass media campaign)
- Refresher training and up-date on WHO/UNICEF guidelines for treatment of childhood diarrhea
- Frequently asked questions booklet
- Follow-up support

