## The training provided by the NGOs will be done through quarterly meetings and follow-up sessions with village practitioners throughout the unions. This work will be done by Sub-Assistant Medical Officers (SACMOs). The SACMOs are graduates of diploma courses at government medical schools. This course includes three full years of study with an additional one year internship. SACMOs are licensed practitioners and are generally used to manage primary health care of patients.

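### The timetable lists training of the NGO's own clinicians above the baseline survey, and nothing in the protocol keeps the intervention-area baseline free of package training

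*Protocol*

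**What the plan says.** The timetable in the Protocol (Conduct of study and timetable) lists seven activities. The second is "Training of SACMOS", the third "Baseline Survey" and the fourth "Training of Private providers". Follow-up support, the endline survey and analysis come after these. The month cells are blank in the text available.

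Other sections describe the SACMOs' role:

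- **Hypothesis to be Tested.** The package is meant to scale up prescribing of "zinc among NGO and private sector providers for the treatment of acute childhood diarrhea will" produce the effects in H1 and H2. NGO prescribing is therefore part of what is tested.
- **Study populations.** NGO SACMOs are listed as health care providers under study.
- **Intervention Package.** "ICDDR,B will first train the trainers, i.e. the NGO health care providers who will implement the intervention package". This places SACMO training ahead of private-provider training and says nothing about the baseline.
- **Orientation package/training program.** One of its two parts is headed "For DSK Health care providers (MBBS & SACMO): provided by ICDDR,B study staff". It covers the diarrhoea treatment guidelines, videos, booklets and follow-up support. No training is listed for GK, the NGO in the control area.
- **Paragraph on training by the NGOs.** "SACMOs are licensed practitioners and are generally used to manage primary health care of patients".

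The protocol gives three time anchors for the effect. The hypothesis expects it within 4 months. Measurement/Data collection tools puts endline six months after baseline. Data Analysis measures change six months after the package is introduced.

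**The concern.** A controlled before-after study needs a baseline that precedes the intervention in both areas. SACMOs are trainers, but they are also treating clinicians who receive the guideline course themselves. The outcome is household coverage among children with diarrhoea in the past two weeks, so zinc prescribed by a newly trained SACMO would count at baseline.

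If that happens, baseline zinc use is too high in the intervention area, and use of antibiotics and antidiarrhoeals may be too low. The control area is not affected, so subtracting its change does not remove the error. The difference in change is biased towards no effect for both H1 and H2. The study asks whether working through NGOs adds value, so the risk is an unduly negative answer. A missed pre-training baseline cannot be collected afterwards.

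**Working it through.** **Step 1: what the order shows.** The rows run in natural time order, from staff training to analysis. On that reading SACMO training comes before the baseline survey, or at least is not held until after it. Because the month marks are lost, the two could share a month or overlap. Overlap would do similar harm for every interview held after training. It is also plausible: baseline means finding 20 active cases in each of 29 villages per group. An endline six months after baseline leaves about two of the eight timetable months for everything else, and about one if the Project Summary's dates (1 November 2007 to 31 May 2008, seven months) apply.

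**Step 2: reproduce the protocol's sample size.** Inputs from Sample size estimation for Survey: Z values 1.64 and 1.28, p = 0.15, d = 0.075, C = 1.5.

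n = (1.64 + 1.28)² × 0.15 × 0.85 × 2 × 1.5 / 0.075² = 579.8, which rounds to the stated 580 per group (29 × 20).

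**Step 3: power from the same formula.** Effective n = 580 / 1.5 = 386.7 per group. Standard error = √(2 × 0.1275 / 386.7) = 0.0257.

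Power = Φ(d / 0.0257 − 1.64). At d = 0.075 this gives 90.0%, as planned. The formula compares two proportions. It is used here as the protocol uses it, not as a formula for a difference in change.

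**Step 4: shift in baseline.** Let s be the share of surveyed cases treated by SACMOs and q their zinc use after training. Then:

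- shift = s × (q − 0.15)
- observed change = 0.075 − shift, with intervention-area endline use held at 22.5%

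The documents give neither s nor q, so both are assumed. For s, Rationale says unlicensed providers make up more than 90% of the preferred source when help is sought. SACMOs are licensed, so they fall in the remaining share of under 10%. That figure describes Bangladesh, not these unions, so 10% is a guide and not a proven local limit.

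With q = 22.5%, the protocol's own 50% relative increase:

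| s | Shift (points) | Observed change (points) | Power |
|---|---|---|---|
| 2% | 0.15 | 7.35 | 89% |
| 5% | 0.38 | 7.13 | 87% |
| 10% | 0.75 | 6.75 | 84% |

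With q = 50%, a much stronger response:

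| s | Shift (points) | Observed change (points) | Power |
|---|---|---|---|
| 2% | 0.70 | 6.80 | 84% |
| 5% | 1.75 | 5.75 | 73% |
| 10% | 3.50 | 4.00 | 47% |

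Both tables treat every baseline episode as falling after SACMO training. If only some do, the shift is smaller in proportion. The protocol states no baseline level for antibiotics or antidiarrhoeals, so the effect on H2 is not quantified.

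**The case against.** The strongest reply is that the sequence is not established. Row order is all that can be read, and the word first in Intervention Package orders SACMO training against private-provider training only. This stands, and it lowers confidence. It does not remove the point, because no sentence elsewhere secures a clean baseline.

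A reader might infer that the intervention has already begun at baseline. The documents do not support that for the main channel. Project Summary and Study Design describe a package delivered by the NGO to private providers, and their training is listed after the baseline. SACMO training is a train-the-trainer step with a side effect on the SACMOs' own patients. Nor does anything say that SACMOs would pass the message on before private-provider training starts; that work runs through quarterly meetings and follow-up sessions.

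A reader might also infer a large bias. If SACMO zinc use rose from 15% to 75%, a 10% share would give 0.10 × 0.60 = 6 points. No such rise appears in the documents. A 10% share is also extreme: the figure applies only when help is sought, the licensed remainder includes government and private providers, and there are eight SACMOs and one medical officer per two unions. SACMOs may also already use zinc more than the 15% assumed, since the existing programme includes orientation of licensed providers.

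Finally, the bias cannot create a false benefit, and a simple comparison of the two areas at endline is untouched. Both are true. However, the planned outcome is change in coverage, which depends on the baseline.

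**Conclusion.** The point holds in a limited form. The timetable's order indicates that SACMO training is not held until after the baseline survey, and the protocol has no rule that baseline be completed first. Any contamination would fall on the intervention area only and bias the change towards no effect.

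The size is unknown and probably modest. Under the protocol's own 50% relative increase it is about 0.75 points of 7.5 at a 10% SACMO share, with power about 84% instead of 90%, and less at smaller shares. It becomes serious only if SACMO prescribing rises far more than that and SACMOs treat a sizeable share of cases.

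This should be fixed but is not a must-fix. Confidence is medium to low, because the sequence is inferred from row order and both the SACMO share and the rise in their prescribing are assumed.

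**What to change.** 1. In Conduct of study and timetable, place the baseline survey in the DSK unions before SACMO training.
2. State that no package training of any provider starts in those unions until their baseline interviews are complete. Survey the DSK villages first to limit the delay.
3. Define the date on which the intervention starts. Reconcile the 4 months in the hypothesis, the six months after baseline in Measurement/Data collection tools, and the six months after introduction in Data Analysis, so that there is one endline date.

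The cost is small. Private-provider training is already listed after baseline, so it moves later only by the time needed to train a small group of SACMOs. If endline stays six months after baseline, exposure before endline is slightly shorter, which itself leans towards no effect and should be weighed when the dates are set. No extra staff or participants are needed.

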## Facilities Available

Describe the availability of physical facilities at the place where the study will be carried out. For clinical and laboratory-based studies, indicate the provision of hospital and other types of patient’s care facilities and adequate laboratory support. Point out the laboratory facilities and major equipment that will be required for the study. For field studies, describe the field area including its size, population, and means of communications.

ICDDR,B has a long-standing reputation of carrying out collaborative research with various national and international institutions. HSID has a good contingent of investigators, support staff, data management staff and field research staff experienced in conducting operations research. This study will be done in collaboration with Plan International and its partner NGOs, Dushtha Shasthya Kendra (DSK) and Gonoshasthya Kendra (GK). Each of these NGOs has a physical infrastructure that includes a field office, fixed and satellite service delivery points and outreach. All information regarding service providers list, coverage by service, location and total household numbers of the two catchments areas are available within these field offices. The proposed study fits well with the existing facilities of the collaborating NGOs.

## Data Safety Monitoring Plan (DSMP)

All clinical investigations (biomedical and behavioural intervention research protocols) should include the Data and Safety Monitoring Plan (DSMP) to provide the overall framework for the research protocol’s data and safety monitoring. It is not necessary that the DSMP covers all possible aspects of each elements. When designing an appropriate DSMP, the following should be kept in mind.

1. All investigations require monitoring;
2. The benefits of the investigation should outweigh the risks;
3. The monitoring plan should commensurate with risk; and
4. Monitoring should be with the size and complexity of the investigation.

Safety monitoring is defined as any process during clinical trails that involves the review of accumulated outcome data for groups of patients to determine if any treatment procedure practised should be altered or not.

Not applicable

## Data Analysis

Describe plans for data analysis. Indicate whether data will be analyzed by the investigators themselves or by other professionals. Specify what statistical software packages will be used and if the study is blinded, when the code will be opened. For clinical trials, indicate if interim data analysis will be required to monitor further progress of the study.

The investigative team will carry out the data analysis. Data entry and general management will be done by Data Resources and Surveillance Unit of the Division. Data will be entered and analyzed using SPSS version 12.0. Absolute counts, proportions, and means with 95% confidence interval will be calculated. These and regression analysis will be done using STATA version 9, cluster survey program, that accounts for potential within cluster homogeneity.

Based upon the household surveys, the following outcomes will be calculated:

- Coverage: the proportion receiving zinc, ORS (zinc and ORS), and antibiotics or antidiarrhoeals and changes in coverage 6 months following the introduction of the intervention package.
- Equity: who is receiving zinc by age, gender and socioeconomic status
- For differences in categorical outcomes crude relative risks and 95% confidence intervals will be determined.

The provider interviews will be recorded and transcripts prepared. Qualitative responses will be sub-grouped by topic and response.

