**Rationale:**

In order to reach all children with diarrhoea, zinc treatment will need to be introduced and sustained within public, NGO and private service delivery systems. To improve zinc coverage, the Ministry of Health and Family Welfare (MOHFW) has initiated a program within the public sector that aims to distribute zinc, free of charge as a treatment of childhood diarrhea. However, a large population of the country, mostly the poor are served by NGO health services. Plan International, Bangladesh has been working for many years with children and families in some of the poorest communities, with aim of improving the quality of their lives, including their health. Across Bangladesh Plan works with 30 partner NGOs who provide community based services. These NGOs are highly respected within the communities they work, both among the general population and health providers. Whether these NGOs can significantly impact the diarrhoea treatment practices of private providers is unclear and should not be assumed. Past work carried out by the SUZY team with NSDP service providers plus local community sensitization and zinc promotion was not successful in improving zinc treatment coverage. The Plan model of having NGOs work with local providers is an alternative that deserves attention and validation of impact.

In Bangladesh, health seeking for childhood diarrhoea is dominated by utilization of private sector providers (18). Unlicensed providers (village doctors, drug sellers, and homeopaths) comprise more than 90% of the preferred source of care when help is sought.

The proposed study will be carried out in a rural community, where Dushtho Sasthya Kendra (DSK) [intervention area] and Ganosasthyo Kendra (GK) [control area], two partner NGOs of Plan International provide primary health care services along with other programs in Gazipur district, located north of Dhaka.

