The proposed study will assess the impact of a zinc scale up intervention package that entails strong and sustained NGO-private sector collaboration. The aim is to build upon the existing mass media and provider promotion campaigns already implemented in Bangladesh, in the hope that this additional collaboration will maximize zinc treatment coverage for acute childhood diarrhoea (ACD). The impact of the zinc scale up package on inappropriate prescription/sale of antibiotics will also be assessed. The proposed study will assess the impact of a zinc scale up intervention package that entails strong and sustained NGO-private sector collaboration. We will determine whether the effort and expense of scaling up specifically with NGOs provides value added to the nation-wide programs described above as well as other changes to the public health system.

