**Research Design and Methods**

Describe in detail the methods and procedures that will be used to accomplish the objectives and specific aims of the project. Discuss the alternative methods that are available and justify the use of the method proposed in the study. Justify the scientific validity of the methodological approach (biomedical, social, or environmental) as an investigation tool to achieve the specific aims. Discuss the limitations and difficulties of the proposed procedures and sufficiently justify the use of them. Discuss the ethical issues related to biomedical and social research for employing special procedures, such as invasive procedures in sick children, use of isotopes or any other hazardous materials, or social questionnaires relating to individual privacy. Point out safety procedures to be observed for protection of individuals during any situations or materials that may be injurious to human health. The methodology section should be sufficiently descriptive to allow the reviewers to make valid and unambiguous assessment of the project.

**Study Design:** This will be controlled before-after (CBA) study. An equivalent control area will be included in the study. The objective is to document changes in zinc and antibiotic as well as anti-diarrhoeal usage in childhood diarrhoea following a scale-up intervention package delivered by a local NGO to local private providers. This will include sensitization, training and follow-up support. Impact will be assessed in terms of changes in zinc coverage and antibiotic use among households in the catchment population served by these providers.

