## Study sites: The study will be conducted in four unions located in Sreepur Upazila within Gazipur district, located north to Dhaka. Two of the unions, namely Rajabari and Prohladpur comprising 55 villages with 15,530 households and an estimated 76,150 population will serve as intervention area. The other two unions Telihat and Barmi will be taken as control sites. They contain 53 villages with 19,898 households and an estimated 99,000 population. Local drug vendors, village practitioners, traditional healers, and licensed government, private or NGO health service providers provide the curative health services in these sites.

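### The only between-condition effect measure specified is a crude relative risk, which cannot separate the NGO package from shared national trend or from baseline differences between the areas

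*Protocol*

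**What the plan says.** Research Design and Methods sets the design: "This will be controlled before-after (CBA) study. An equivalent control area will be included in the study". Under Study sites, "Two of the unions, namely Rajabari and Prohladpur comprising 55 villages with 15,530 households and an estimated 76,150 population will serve as intervention area", and two other unions of the same upazila serve as control. No random assignment of areas is described, and the Rationale places a different partner NGO in each area.

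The Rationale asks whether scaling up through NGOs "provides value added to the nation-wide programs described above". Those programmes are current: the section on scaling up zinc lists mass media, sales-representative promotion and training workshops for village doctors, and the Rationale adds that the health ministry "has initiated a program within the public sector that aims to distribute zinc, free of charge".

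Data Analysis, whose content is repeated in the Project Summary, names three relevant items:
- an outcome described as "changes in coverage 6 months following the introduction of the intervention package", alongside the coverage proportions;
- software and variance method: "These and regression analysis will be done using STATA version 9, cluster survey program, that accounts for potential within cluster homogeneity";
- the effect measure: "For differences in categorical outcomes crude relative risks and 95% confidence intervals will be determined".

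H1 predicts a rise in zinc coverage inside the NGO catchment and names no comparison with the control area. The sample size formula is a single two-proportion contrast, 15% against 22.5%.

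**The concern.** A controlled before-after study has four samples: two areas at two rounds. A crude relative risk contrasts two of them. Endline against baseline in the intervention area leaves out what happened in the control area over the same six months, so national promotion counts as intervention effect. Intervention against control at endline leaves out where the two areas started, so any existing difference between them counts as effect.

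The stated question is value added over a moving national background. Only a comparison of the two areas' changes addresses it, and the protocol does not state that comparison in the hypothesis, the sample size formula or the analysis. If a crude relative risk is presented as impact, the NGO package could be credited with the national campaign's effect. The same applies in the other direction to antibiotic and antidiarrhoeal use under H2.

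**Working it through.** **Inputs from the protocol (sample size section):** baseline p = 0.15, d = 0.075, one-sided z = 1.64, power z = 1.28, design effect C = 1.5, 29 villages × 20 children per group. The cover form's 1160 at baseline and endline is read as 580 per area in each round.

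**Inputs assumed:** the size of any shared trend or baseline gap. The protocol gives neither, so a range is shown.

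**1. The plan's own figure.** n = (1.64 + 1.28)² × 0.1275 × 2 × 1.5 / 0.075² = 579.8, which reproduces 580; 580/20 = 29 villages. The arithmetic is right, for one two-group contrast.

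**2. Crude before-after comparison, no intervention effect, shared trend.** SE = √{[p₀(1−p₀) + p₁(1−p₁)] × 1.5/580}.
- 15% to 20% (RR 1.33): SE = √[(0.1275 + 0.1600) × 1.5/580] = 0.0273; z = 0.05/0.0273 = 1.83. Declared an increase with probability Φ(1.83 − 1.96) = 0.45 two-sided, or Φ(1.83 − 1.645) = 0.57 one-sided.
- 15% to 18% (RR 1.20): SE = √[(0.1275 + 0.1476) × 1.5/580] = 0.0267; z = 1.12. Probabilities 0.20 and 0.30.

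On the log relative risk scale, with effective size 580/1.5 = 387 per sample, the 15% to 20% case gives z = 1.82 and 0.44 two-sided; the 15% to 18% case again gives 0.20.

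**3. Crude endline comparison, no change over time, fixed gap.** The same two proportions enter, so a standing 20% versus 15% gap between areas also gives about 0.44 two-sided on the log scale.

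**4. Area-by-round contrast.** In simulation (200,000 draws per scenario, 387 per sample, no intervention effect) with a shared rise from 15% to 20% or 22.5%, or a fixed gap of 20% or 22.5% versus 15%, both the risk difference-in-differences and the ratio of relative risks rejected in about 5% of studies, two-sided.

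**5. What that contrast costs in power.** True effect 15% to 22.5% in the intervention area, control area flat at 15%.
- Difference-in-differences: SE = √[(3 × 0.1275 + 0.1744) × 1.5/580] = 0.038; 0.075/0.038 = 1.98. Power Φ(1.98 − 1.645) = 63% one-sided, Φ(1.98 − 1.96) = 51% two-sided.
- Ratio of relative risks: SE = √[3 × 0.85/(387 × 0.15) + 0.775/(387 × 0.225)] = 0.230; ln 1.5/0.230 = 1.76. Power about 55% one-sided, 42% two-sided.
- Part of the gap from 90% arises because the plan's formula uses the baseline variance in both groups. With each group's own variance, the single contrast has z = 0.075/√[(0.1275 + 0.1744) × 1.5/580] = 2.68, or about 85% one-sided.
- The plan's formula with four samples instead of two doubles n to about 1,160 per area per round (about 1,266 with each sample's own variance).
- If 1160 were the total over both rounds (290 per area per round), difference-in-differences power would be about 40% one-sided.

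**The case against.** The strongest reply is that the plan does not rest on the crude relative risk alone. Change in coverage is a listed outcome, the Study Design paragraph says impact will be assessed through changes in zinc coverage and antibiotic use, a control area is built in, and a cluster-aware regression is announced. The crude relative risk comes in the last bullet of the outcome list, is not called primary, and may be only the unadjusted companion to that regression. The model's terms and covariates are details that a separate analysis plan could supply.

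Much of this stands. A reader might infer that the plan contains no other quantity, that it discards the control area or the baseline survey, or that it cannot answer its question at all. The text supports none of these: nothing limits the analysis to one relative risk, and reporting by area and round would use all four samples. A reader might also infer that adjustment is ruled out because age, gender and socioeconomic status appear only under equity. That reads a restriction into silence, since the regression is not confined to unadjusted models.

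The reply does not remove the stated method. Where the protocol does say how differences will be measured, it says crude relative risk; the hypothesis and the sample size formula also describe a single contrast, and change is nowhere set against the control area's change.

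**Conclusion.** The concern holds in this form: the one between-condition effect measure specified can give a wrong answer to the protocol's own question, and the items that might correct it are not defined to do so. With no intervention effect, an assumed shared rise of 3 or 5 points would produce a significant crude before-after result in about 20% or 45% of studies two-sided, against a nominal false-positive rate of 5%. Those sizes are illustrations. They rest on the assumed trend, on 580 per area per round, and on the protocol's design effect of 1.5. The direction of the bias does not depend on them.

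A reader might also infer that switching to the area-by-round contrast settles attribution. It removes shared trend and fixed area differences. With two unions per arm it cannot rule out a trend specific to one area.

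**What to change.** State that the primary analysis for H1 and H2 is the area-by-round contrast, expressed as either a risk difference-in-differences or a ratio of relative risks, with the scale chosen in advance. Estimate it from one survey regression over all four samples, clustered on village, and adjust for child age, sex and socioeconomic status, which the plan already uses for equity. Keep crude relative risks as description.

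The model needs no new data items and runs in the Stata survey commands already planned. The real cost is precision. The 90% power statement must be restated for this contrast: either accept and report the lower power at 580 per area per round, or enlarge the sample, for which the protocol's own formula points to about 1,160 per area per round. This should be settled before fieldwork. The limitation of two unions per arm should be acknowledged alongside the result.
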